### Statistical analysis

The SPSS 23.0 software will be used for data processing and statistical analysis. Descriptive statistics will be used to process sociodemographic data, of which observable variables are presented as the means ± standard deviations for continuous variables and frequencies and percentages for categorical variables. Exploratory analysis will be applied to examine the distribution of data. Baseline data comparisons between the two groups will be conducted using the chi–square (*χ*^2^) test (for categorical variables) and *t-test* or Wilcoxon rank-sum test (for continuous variables). 2(group)× 3(time) ANOVA is used for data with a normal distribution and homogeneity of variance, and a generalized estimation equation is used for data with a nonnormal distribution to determine the main effect of intervention factors, time factors, and interaction between group factors and time factors. Simple effects will be further analyzed when there are interaction effects. A two-tailed *P* < 0.05 will be considered statistically significant.

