**Methods:**

This study is a randomized controlled trial (RCT). One of the municipal districts in Huzhou, China, will be randomly selected, and two communities with similar conditions within this district will be screened and selected. A total of 120 hypertensive patients aged 18 years and older will be recruited from these two community settings. One of the communities will be randomly allocated to an interactive pictorial health education program conducted by a comprehensive health literacy strategy that includes (i) training participants in effective health communication skills that address issues encountered in seeking medical care and (ii) the use of self-developed interactive pictorial hypertension education to improve patient understanding and behaviors versus a control group (routine community lecture health education only). The primary outcome measure is HBP-HL. Secondary outcomes are self-efficacy, self-management ability, HRQOL, social support, and improvement in blood pressure. Outcomes will be collected at 6, 9, and 12 months from trial entry.

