### Clinical measurements

Blood pressure will be measured by the same surveyor with an Omron HEM-7211 electronic sphygmomanometer after the patient has rested quietly for at least 5 min. The measurement will be repeated at intervals of at least 5 min, and the average of the two readings will be recorded.

Anthropometric measurements, including height (cm), weight (kg), neck circumference (NC) (cm), waist circumference (WC) (cm), and hip circumference (cm), will be measured by researchers for all participants in lightweight clothing and bare feet. Body weight will be obtained using an Omron HBF-214 electronic scale, height will be reported by participants, and NC, WC, and hip circumference will be measured using a clinical tape measure. The parameters will be measured and recorded to the nearest 0.1 cm or 0.1 kg. Body mass index (BMI) is referred to as weight (kg)/height (m)^2^. According to the Working Group on Obesity in China, BMI is divided into normal weight (18.5 ≤ BMI < 24 kg/m^2^), overweight (24 ≤ BMI < 28 kg/m^2^), and obesity (BMI ≥ 28 kg/m^2^) [35]. NC is determined by measuring the horizontal circumference of the neck between the lower margin of the thyroid cartilage (Adam's apple) and the upper margin of the 7th cervical vertebra. WC is measured at the midpoint between the lateral anterior superior iliac spine and the lower border of the tenth rib. Using criteria from the WHO for the Chinese population, a WC ≥ 90 cm for men and ≥ 80 cm for women is considered abdominal obesity [36].

Measurements will be taken at baseline and at 6, 9, and 12 months from trial entry **(**the detailed timeline is shown in Table 2). To decrease the dropout rate, some retention strategies will be carried out: (1) collecting contact information of participants and their family members, (2) distributing a gift for every participant at each event, and (3) providing a quiet and comfortable environment for the intervention. In addition, the measurements will be collected by designated and appropriately trained and blinded assessors.

**Table 2 Tab2:** Summary of study assessments and timelines

Questionnaire items		Time point				
		Baseline T0	Randomized Allocation	The 6th month of intervention T1	The 9th month of intervention T2	Follow-up 3 months T3
Enrollment Eligibility screening Informed consent Screening						
Primary outcomes	C-HBP-HLS	√		√	√	√
Secondary outcomes	CDSMP	√		√	√	√
	HPSMBRS	√		√	√	√
	Perceived social support scale	√		√	√	√

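### The ANOVA has three time levels for four scheduled visits; neither the visits nor the term that tests treatment is stated, and no baseline adjustment is given

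*Protocol article*

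**What the plan says.** The Abstract (Methods) states that "The primary outcome measure is HBP-HL". For the between-group analysis, the Statistical analysis section says that "2(group)× 3(time) ANOVA is used for data with a normal distribution and homogeneity of variance", with a generalized estimating equation for non-normal data. The purpose is "to determine the main effect of intervention factors, time factors, and interaction between group factors and time factors". It adds that "Simple effects will be further analyzed when there are interaction effects". The three time levels are not named, and no term is singled out as the test of treatment.

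The schedule has four visits. The Clinical measurements section says "Measurements will be taken at baseline and at 6, 9, and 12 months from trial entry". Table 2 ticks C-HBP-HLS and every secondary outcome at T0, T1, T2 and the column headed "Follow-up 3 months T3". The Abstract counts differently and lists only post-baseline visits: "Outcomes will be collected at 6, 9, and 12 months from trial entry".

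Baseline appears in the analysis only as a separate test: "Baseline data comparisons between the two groups will be conducted using the chi–square" and related tests. No baseline covariate is stated. Under Setting and Sequence generation, each arm is one community. The pair is screened for similar size, education and income.

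**The concern.** Three levels cannot hold four visits, so the one layout the article states leaves a visit out. Together with its GEE alternative, this is the only between-group outcome analysis described, so it governs the primary outcome.

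The choice of visits decides which term measures treatment. With T0 among the levels, the interaction does. With T1 to T3 only, the group main effect does, and the interaction asks merely whether the difference changes between 6 and 12 months. An analyst who looks at the wrong term for the layout gets either a diluted estimate or a test with almost no power.

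Baseline deserves more care here than in an individually randomised trial. Randomising two communities cannot be expected to balance HBP-HL between arms, and a baseline significance test corrects nothing.

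**Working it through.** **Inputs.** From Sample size calculation: pilot means 32.09 and 27.80, stated effect size 0.405, 108 participants before dropout (54 per group). From Statistical analysis: 2 groups, 3 time levels. From Table 2: 4 visits. Assumed, because the documents give no values: a true effect *d* that is zero at T0 and constant afterwards, compound symmetry, and a correlation ρ between visits of 0.3, 0.5 or 0.7. Clustering is ignored.

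**Step 1, the count.** Four visits minus three levels leaves one visit outside the model.

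**Step 2, what the group main effect estimates.** It is the mean of the visit-specific group differences.

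- Pilot difference: 32.09 − 27.80 = 4.29 points.
- T1 to T3: (*d* + *d* + *d*)/3 = *d*, or 4.29 points.
- T0 and any two later visits: (0 + *d* + *d*)/3 = 0.667*d*, or 2.86 points.

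**Step 3, a stable community offset *b*.**

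- Group main effect, T1 to T3: *d* + *b*.
- Group main effect, T0 as a level: (*b* + *b* + *d* + *b* + *d*)/3 = 0.667*d* + *b*. The offset is in the main effect here too.
- Group-by-time contrast from T0: (*d* + *b*) − *b* = *d*. A stable offset cancels.
- T0 as a covariate: *d* + *b*(1 − ρ), since under compound symmetry the slope on T0 is ρ. For ρ = 0.3, 0.5 and 0.7, 70%, 50% and 30% of the offset remains.

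The documents give no value for *b*. For assumed offsets of 1, 2 and 3 points, *b*/4.29 is 23%, 47% and 70% of the pilot difference.

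**Step 4, power by term.** With *n* = 54 per group, *m* levels and an effect of 0.405 SD at each post-baseline visit, the noncentrality is

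- group: λ = (*n*/2) × mean² / [(1 + (*m* − 1)ρ)/*m*];
- interaction: λ = (*n*/2) × Σ(deviation from mean)² / (1 − ρ).

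Example at ρ = 0.5. Group, T0 to T2: 27 × 0.270² / 0.667 = 2.95. Group, T1 to T3: 27 × 0.405² / 0.667 = 6.64. Interaction, T0 to T2: 27 × (0.270² + 2 × 0.135²) / 0.5 = 5.90. Interaction, T1 to T3: all deviations are zero, so λ = 0 and power equals the 5% test level for any *d* and ρ.

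| Layout | Term | ρ = 0.3 | ρ = 0.5 | ρ = 0.7 |
|---|---|---|---|---|
| T0, T1, T2 | group | 48% | 40% | 34% |
| T0, T1, T2 | interaction | 43% | 57% | 80% |
| T1, T2, T3 | group | 82% | 72% | 65% |
| T1, T2, T3 | interaction | 5% | 5% | 5% |

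These figures compare layouts and do not forecast this trial's power. They take 0.405 as a difference in SD units. The pilot values themselves give 4.29/4.835 = 0.887 SD, and the stated 108 does not follow from the stated inputs alone. That is a separate matter and does not affect Steps 1 to 3.

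**The case against.** The best defence is that the text already points to T1 to T3. The Abstract lists exactly three outcome times, and baseline is compared in its own test. On that reading nothing after baseline is lost and the group main effect is undiluted. This is a fair reading and probably the intended one. It is not stated, however. The sample-size section describes a pre-test and post-test design and the hypotheses speak of improvement, which point the other way. The T1 to T3 reading is also the one with no baseline term.

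A second defence is that an article may leave the contrast and the covariates to an analysis plan. That covers missing detail. It does not cover a stated number of levels that disagrees with the stated schedule.

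Third, the article says under Strengths and limitations that cases will be matched. Matching on HBP-HL would shrink the offset, but no matching variables are given, and the communities are screened on other features.

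Several stronger readings are tempting and not supported:

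- *The 12-month visit is dropped.* Nothing says so, and leaving out 6 or 9 months would also give three levels.
- *The group main effect is not the treatment effect.* This is true only if T0 is a level.
- *The main effect is the deciding test, or either term may claim success.* The plan lists the usual ANOVA terms, includes the interaction and states no success criterion.
- *Omitting T0 is what lets a community offset in.* Step 3 shows that the offset enters the group main effect in either layout.

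**Conclusion.** The concern holds as an internal mismatch with a consequence for the primary outcome: three time levels against four visits, with the visits and the treatment term unstated. On the favoured T1 to T3 reading, the group main effect is the right size for a constant effect, but it carries any stable community difference in full, and the interaction is uninformative (5% power). If T0 is a level, the main effect shrinks to two thirds (2.86 of 4.29 points) and the interaction becomes the relevant test.

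The two-thirds figure rests on an effect that is constant after baseline. The other power figures also rest on the assumed correlations and on 0.405 SD. The size of any community offset is unknown.

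**What to change.** Replace the ANOVA sentence so that it names the visits, the term and the baseline handling:

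- **Preferred:** keep T1, T2 and T3 as the three time levels, enter T0 as a covariate, and name the baseline-adjusted group effect as the primary test of HBP-HL.
- **Alternative:** fit 2(group) × 4(time) and name one group-by-time contrast from T0 as the primary test, stating which later visit or average of visits it uses.

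The two answer slightly different questions. The covariate removes part of a stable offset, and the contrast cancels it, so the authors should choose one before outcomes are analysed. The GEE alternative should carry the same specification. In any model with T0 as a level, the group main effect should not be read as the treatment effect.

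The cost is one sentence, and every measurement needed is already scheduled. The change reduces bias from baseline differences. It does not separate treatment from community, because each arm is a single community in any layout, and the report should say so.

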### Randomization and blinding

#### Sequence generation

After completing the screening of the two communities with similar size, educational background and economic income, randomization will be performed at the level of the community after recruitment is completed. One community will be randomized to receive the intervention, and the other community will be randomized to the control group by throwing dice. The randomization process will be completed by a third party unrelated to the study. Only after the subjects have completed the baseline data collection, the allocation personnel can inform the researchers of the allocation results.

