### Outcomes and measuring instruments

#### Sociodemographic questionnaire

The questionnaire is a self-administered survey including age, gender, education, occupation, financial status, marital status, living condition, insurance status, smoking and alcohol status, history of hypertension, family history of hypertension, types of blood pressure medications, self-test blood pressure status, and complications.

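### The analysis of C-HBP-HLS is chosen between ANOVA and GEE by the observed distribution, names no baseline covariate, and has a three-level time factor that does not fit the four assessments.

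*Protocol article*

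**What the plan says.** The Statistical analysis section sets a rule that starts from the data: "Exploratory analysis will be applied to examine the distribution of data". One branch is "2(group)× 3(time) ANOVA is used for data with a normal distribution and homogeneity of variance". In the other, "a generalized estimation equation is used for data with a nonnormal distribution". Both serve "to determine the main effect of intervention factors, time factors, and interaction between group factors and time factors". No covariate is named. The rule covers all outcomes, and so the primary one, C-HBP-HLS.

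The only stated use of baseline in comparing the arms is a set of significance tests ("Baseline data comparisons between the two groups will be conducted using the chi–square" test, t-test or rank-sum test), and nothing in the model follows from their result.

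Allocation is by community, one per arm: "randomization will be performed at the level of the community after recruitment is completed" (Sequence generation). The same section completes baseline collection before the allocation is disclosed. Baseline covariates are at hand: "The questionnaire is a self-administered survey including age, gender, education, occupation, financial status" and more (Sociodemographic questionnaire). Table 2 lists C-HBP-HLS at T0, T1, T2 and T3, which is four assessments.

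**The concern.** Three features of the same few sentences cause trouble together.

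- **Choice of method.** The analysis of the primary outcome is not known until the data have been inspected. The reason for switching is weak. With the usual identity link, GEE estimates the same difference in means as the ANOVA, and at about 54 per arm a comparison of means does not need normal data. The rule also has a gap: normal data with unequal variances fall in neither branch.
- **No baseline term.** With one community per arm, randomisation cannot balance individual characteristics. A non-significant baseline test at this size does not show balance, and the baseline score would buy precision in any case.
- **Three time levels against four assessments.** The sentence does not say which visit is left out, and the role of baseline depends on that.

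At stake are the precision of the primary comparison, possibly its bias, and whether the primary result is fixed in advance.

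**Working it through.** **Inputs from the protocol article.** Sample size calculation: pilot scores 32.09 ± 4.89 and 27.80 ± 4.78, a difference of 4.29 points; 108 participants before dropout, so 54 per arm. The dropout step reproduces: 108 / 0.9 = 120. The plan gives no figure for the gain from baseline adjustment.

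**Assumptions.** The documents give no correlation ρ between baseline and follow-up scores. I take 0.5 to 0.7, with 0.3 as a low case. The retest reliability of 0.96 points upward; the entry limit of a score below 40 points downward. SDs are taken as equal at all visits and participants as independent, so variation between communities is left out.

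**1. Single-visit standard error of the arm difference**

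Pooled SD = √((4.89² + 4.78²)/2) = 4.835. Unadjusted SE = 4.835 × √(2/54) = 0.93. Adjusting for baseline multiplies it by √(1 − ρ²); using change from baseline multiplies it by √(2(1 − ρ)).

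| ρ | Unadjusted | Change from baseline | Baseline-adjusted |
|---|---|---|---|
| 0.3 | 0.93 | 0.93 × √1.40 = 1.10 | 0.93 × √0.91 = 0.89 |
| 0.5 | 0.93 | 0.93 × √1.00 = 0.93 | 0.93 × √0.75 = 0.81 |
| 0.7 | 0.93 | 0.93 × √0.60 = 0.72 | 0.93 × √0.51 = 0.66 |

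Adjustment is the most precise of the three in every row.

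**2. The two readings of the time factor**

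- *Levels are 6, 9 and 12 months.* Baseline is unused, and any community imbalance enters the group effect.
- *Baseline is one of the three levels.* The interaction compares changes. If one community sits g points higher throughout, its change is (follow-up + g) − (baseline + g), so g cancels. However, one post-baseline visit is dropped, the group main effect is diluted by a pre-treatment value, and precision is lost as in the change column.

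**3. What adjustment does to an imbalance (first reading)**

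Take an illustrative 2-point baseline imbalance, against the pilot difference of 4.29.

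- Chance imbalance: the unadjusted comparison carries ρ × 2 = 1.0 (ρ = 0.5) to 1.4 points (ρ = 0.7), which adjustment removes.
- Lasting community gap: the unadjusted comparison carries all 2 points. Adjustment removes ρ × 2 and leaves (1 − ρ) × 2 = 1.0 to 0.6 points.

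A simulation (54 per arm, 2,000 runs per setting, no treatment effect, an assumed lasting gap of 0.3 SD, or 0.3 × 4.835 = 1.45 points) agrees. The post-baseline group test rejects 48% of the time unadjusted and 22% adjusted at ρ = 0.5, and 41% and 12% at ρ = 0.7. The nominal level is 5%.

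**4. Cost of letting the data choose the model**

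The protocol names no test, so I assume Shapiro-Wilk at 5% in each of six arm-by-visit cells. Were the cells independent, truly normal data would fail at least once with probability 1 − 0.95⁶ = 26%; in simulation about a quarter of normal datasets went to the robust branch. With no community gap, the type I error of the two-stage procedure was 4.5% to 5.0%.

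**The case against.** **This is a condensed article, and a covariate list is commonly left to the analysis plan.** That is fair for a missing list alone. Here, though, the article states a rule, its terms and a number of time levels; the rule is poorly chosen and the number does not fit Table 2. Those points stand.

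**The communities are chosen to be similar.** They are screened on size, education and income, both arms must score below 40, and the strengths section speaks of matching cases. This lowers the expected imbalance. It does not secure balance on individual scores or age, and no individual matching is described. The precision gain does not depend on imbalance at all.

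**A reader might infer that community imbalance must bias the result.** The text does not support this as a certainty. If baseline is one of the three levels, a constant gap drops out of the interaction; the mention of a pre-test and post-test design under Sample size calculation fits that reading. The bias is conditional.

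**A reader might infer that the data-driven choice inflates false positives.** The simulation shows no such cost. The data analyst is also blinded until the analysis is done (Allocation concealment), so the choice is not made with the arms known.

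**A reader might infer that switching models changes how incomplete cases are handled.** The section on dropouts and missing data plans multiple imputation with ten datasets, tied to neither model, so this does not follow.

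**Conclusion.** The point holds, and the text should be changed. The main loss is the missing baseline adjustment: a single-visit standard error of 0.93 points where 0.81 or 0.66 is available at an assumed correlation of 0.5 or 0.7, and 0.89 at 0.3. These figures treat participants as independent, so they understate the true uncertainty with one community per arm.

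The data-driven model choice is the lesser part. It has little type I cost, but it leaves the primary analysis open and serves no inferential purpose. The bias from community imbalance is real only under the reading in which baseline is not a time level, and the wording does not settle that.

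It would be wrong to conclude that adjustment repairs the design. Under an assumed lasting gap of 0.3 SD, 22% or 12% false rejection remains after it.

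**What to change.** - Name one longitudinal model for C-HBP-HLS, used whatever the distribution check shows: the 6-, 9- and 12-month scores as outcome, with arm, visit, arm × visit, the T0 score, age and education, and robust standard errors. This also settles the time factor.
- State the primary visit, for example 9 months, the end of the intervention.
- Report the difference in change from baseline alongside, because individuals are not randomised and a lasting gap between communities is only partly removed by adjustment.
- Keep the baseline table as description, and do not use significance tests to judge balance.
- State that adjustment reduces but cannot remove the confounding of one community per arm.

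The cost is a change of analysis wording, a few degrees of freedom and a little more analysis work. The covariates are already collected, and the named software can fit such a model.

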## Methods

### Study design

This is an RCT (Fig. 2) with a 9-month intervention and a 3-month follow-up. This program will consist of two arms: the intervention group (BCW-based interactive pictorial health education program) and the control group (routine community lecture health education). Prior to the trial, we completed the final draft of the BCW-based interactive pictorial health education program through medical staff and patient interviews and the Delphi method. A pre-experiment was conducted to assess the acceptability and feasibility of the intervention and research procedures in hypertensive patients with low health literacy in Huzhou, Zhejiang, China. We obtained informed consent from each study participant. The results of the two studies have been used to inform the development of the forthcoming trial.

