#### Sample size calculation

The Gpower3.1.9.2 software was used to conduct the sample size calculation. The sample size was estimated by power analysis using the Chinese high blood pressure-health literacy scale for the evaluation of HBP-HL as a primary outcome measure of the study. Cohen’s *d* and the effect sizes were calculated for between-group differences of means of the level of HBP-HL using an independent-groups pre-test and post-test design. From the evidence of our pilot study, the HBP-HL score of the intervention group was 32.09 ± 4.89 points, and that of the control group was 27.80 ± 4.78 points, which led to an estimate effect size as 0.405. The analysis, with a two-sided test using *β* = 0.2, *α* = 0.05, two sample *t-test*, and repeated ANOVA, requires a total sample size of 108 participants. Considering a 10% dropout rate, our final sample size comes to 120 participants (60 participants for both the intervention and control groups).

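### Arm comparisons at each visit depend on a group×time interaction, and the three time levels are not named; if they are 6, 9 and 12 months, a steady benefit meets that condition only about 5% of the time

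*Protocol article*

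**What the plan says.** The Statistical analysis section states that "2(group)× 3(time) ANOVA is used for data with a normal distribution and homogeneity of variance", with generalized estimating equations for non-normal data. Either model is used "to determine the main effect of intervention factors, time factors, and interaction between group factors and time factors". The follow-on rule is "Simple effects will be further analyzed when there are interaction effects", and the only threshold given is "A two-tailed *P* < 0.05 will be considered statistically significant". So a visit-specific comparison of the arms follows a significant interaction, and no other post-baseline comparison by visit is described. No primary time point is named for the health-literacy score.

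The three time levels are not identified. The Abstract lists three occasions, all after baseline: "Outcomes will be collected at 6, 9, and 12 months from trial entry". The Clinical measurements section and Table 2 list four: "Measurements will be taken at baseline and at 6, 9, and 12 months from trial entry". The Study design section describes the structure these visits serve: "This is an RCT (Fig. 2) with a 9-month intervention and a 3-month follow-up".

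**The concern.** A simple effect asks whether the arms differ at one visit; its null is a zero difference at that visit. The group×time interaction asks whether the arm difference changes between visits; its null is the same difference at every modelled visit. The second question is a poor condition for asking the first. With 6, 9 and 12 months as the levels, a programme that works equally well at every visit satisfies the interaction's null exactly, however large its effect.

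At stake are the two results the design is built to give: the difference at the end of the 9-month programme and the difference after 3 further months. If the benefit partly fades and the interaction is missed, only an average over visits remains, and that average is larger than the true 12-month difference.

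**Working it through.** **Inputs.** From the Sample size calculation section: 108 participants before dropout, so 54 per arm (108/0.9 = 120 reproduces the final total); two-sided α = 0.05; a stated effect size of 0.405; and pilot scores: "the HBP-HL score of the intervention group was 32.09 ± 4.89 points, and that of the control group was 27.80 ± 4.78 points". From those scores the pooled SD is √((4.89² + 4.78²)/2) = 4.835 and d = (32.09 − 27.80)/4.835 = 0.887. The stated 0.405 is not this d, so both values are carried through; why they differ is a separate matter. The protocol gives no correlation between visits. I assume a common correlation ρ of 0.3 to 0.8. Participants are treated as independent, as in the protocol's own calculation.

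**Interaction test.** With N = 108, three levels and arm differences δ₁, δ₂, δ₃ in SD units, the F test has (2, 212) degrees of freedom and non-centrality λ = (N/4)·Σ(δⱼ − δ̄)²/(1 − ρ), where N/4 = 27.

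- Steady (d, d, d): the sum is 0, so λ = 0 and the rejection rate is 5% for any d and ρ.
- Half lost at the last visit (d, d, d/2): the sum is d²/6, so λ = 4.5d²/(1 − ρ). For d = 0.405 and ρ = 0.5, λ = 4.5 × 0.1640/0.5 = 1.48.
- Wholly lost at the last visit (d, d, 0): the sum is 2d²/3, so λ = 18d²/(1 − ρ).
- Baseline as a level with a steady benefit afterwards (0, d, d): the same sum, so the same λ as a complete fade.

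Probability that the interaction is significant, so that simple effects are analysed:

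| Pattern | d | ρ = 0.3 | 0.5 | 0.7 | 0.8 |
|---|---|---|---|---|---|
| d, d, d | either | 5% | 5% | 5% | 5% |
| d, d, d/2 | 0.405 | 14% | 17% | 27% | 38% |
| d, d, d/2 | 0.887 | 50% | 65% | 87% | 97% |
| d, d, 0 or 0, d, d | 0.405 | 43% | 57% | 80% | 94% |
| d, d, 0 or 0, d, d | 0.887 | 98.5% | 99.9% | ~100% | ~100% |

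A simulation (4,000 runs, d = 0.405, ρ = 0.5) gave 5.2% for the steady pattern and 16.6% for the half fade, against 5.0% and 17.4% by formula.

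**The same visit without the condition.** A two-sample t-test with 54 per arm has non-centrality d√27: 2.10 for d = 0.405 (power 55%) and 4.61 for d = 0.887 (power 99.5%).

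**What is left when the interaction is missed.** After a half fade the averaged effect is (d + d + d/2)/3 = 0.833d against a true 12-month effect of 0.5d, or 1.67 times as large. At d = 0.405 that is 0.34 against 0.20 SD.

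**How often a fade would leave only a significant average.** This needs a significant group effect and a missed interaction. The group effect has λ = 27·δ̄²/((1 + 2ρ)/3), and under a common correlation the two tests use independent parts of the data, so the probabilities multiply. For d = 0.405, half fade, ρ = 0.5: 0.567 × (1 − 0.174) = 0.47. Over ρ = 0.3 to 0.8 the joint probability falls from 57% to 29% at d = 0.405 and from 50% to 3% at d = 0.887. For a complete fade it is at most 27% (0.478 × 0.570, at d = 0.405 and ρ = 0.3).

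**The case against.** The strongest reply is that baseline may be one of the three levels. The sample-size section speaks of a design with pre- and post-tests, and no baseline covariate is mentioned, so otherwise baseline would not enter the stated model at all. On that reading a steady benefit is itself an interaction and the condition is close to the treatment test: it is met in 43–94% of trials at d = 0.405 and at least 98.5% at d = 0.887. This stands as a limit on the point. The Abstract's three post-baseline outcome times make the other reading somewhat better supported, but the text does not settle it.

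Second, the group main effect is tested unconditionally. A reader might infer that a steady benefit would go undetected. The documents do not support that: at d = 0.405 the averaged test has 61–81% power over the same correlations, more than the 55% of a single-visit test, and under a truly constant effect the average also estimates the 12-month difference without bias. What is lost is the direct evidence by visit.

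Third, a reader might infer that a fading benefit would usually be reported as constant. That is too strong. The joint probabilities above exceed one half only for a partial fade at a modest effect and low correlation, and a complete fade is mostly detected. Nor does the protocol say that a non-significant interaction will be read as proof of constancy, or that visit means and intervals will be left out of the tables; an article may leave those to the full plan.

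Fourth, following an interaction with simple effects is conventional and restrains uncorrected testing visit by visit. That is true, but it does not make the interaction's null match the question about month 9 or month 12.

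**Conclusion.** The point holds conditionally. The rule is stated affirmatively and the time levels are left open. On the 6-, 9- and 12-month reading, a steady benefit of any size would have its visit-specific comparisons analysed in about 5% of trials; this figure does not depend on the assumed correlation or effect size. A half fade by month 12 would be missed in 62–86% of trials at the stated effect of 0.405 and in 3–50% at the pilot value of 0.887, leaving an average that overstates the 12-month difference by two thirds. A complete fade is mostly detected, except at d = 0.405 with low correlation. The fade figures rest on the assumed range of 0.3–0.8; higher correlation would reduce the misses (at 0.9 and d = 0.405, a half fade is missed in about 33%). With baseline as a level the cost is much smaller. The overall averaged comparison is intact throughout, so severity is minor to moderate.

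**What to change.** Name the three time levels, or four if baseline is to be one, and say how baseline enters the model. Then replace the sentence on simple effects with:

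> The between-group difference at 6, 9 and 12 months, and the change in that difference from 9 to 12 months, will be estimated from the model and reported with 95% confidence intervals whatever the result of the group×time interaction; a non-significant interaction will not be taken to show a constant effect.

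Name one contrast as primary and label the others supportive, because more visit-specific estimates will be shown and this is the one small downside. The change costs a sentence or two and a few contrasts from a model already planned. It needs no further data or participants, and it is sound whichever time levels are chosen.
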